**Screening :**

**Rome III Criteria – Constipation Module**

**Negative Fecal occult blood**

**Fulfil inclusion/ exclusion criteria**

2^ND^ VISIT- WEEK 8

Constipation assessment with GQ

Quality of life assessment with PDQ39

Disease severity assessment with MD S- UPDRS

Non motor symptoms assessment with NMS

Questionnaires

Determination GTT

**13. ETHICAL ISSUES**

There will be no ethical issues on this study as following apply:

Consent from patient who agreed to be enrolled for the study of probiotics

Patients were actively monitored for gastrointestinal disorders (common adverse events)

**14. WORKING SCHEDULE**

**14.1 GANTT CHART**

| 2018 | June | July | August | Sept | Oct | Nov | Dec | Jan | Feb | March |
| --- | --- | --- | --- | --- | --- | --- | --- | --- | --- | --- |
|  |  |  |  |  |  |  |  |  |  |  |
| Ethics application and approval |  |  |  |  |  |  |  |  |  |  |
| Patient recruitment and administration of  probiotics |  |  |  |  |  |  |  |  |  |  |
| Sample (faecal), ITT  faecal, clinical data collection and follow-up |  |  |  |  |  |  |  |  |  |  |
| Data analysis and report writing |  |  |  |  |  |  |  |  |  |  |
| Manuscript writing and publication |  |  |  |  |  |  |  |  |  |  |

**15. ESTIMATION OF COST**

| **ITEMS** | | | **COST (RM)** |
| --- | --- | --- | --- |
|  |  |  |  |
|  |  | **Analysis** |  |
|  | i. | Fecal occult blood test (120X RM 15 ) | 1,800.00 |
|  | ii | Capsule Carmine (120X RM 5 ) | 600.00 |
|  | iii | Probiotics | sponsored |
|  | | |  |
| **Total expenses** | | |  |

37. Dupont WD, Plummer WD: "Power and Sample Size Calculations: A Review and Computer Program", Controlled Clinical Trials 1990; 11:116-28.

| **[figure not shown]** | **THE EFFECTIVENESS OF PROBIOTICS**  **IN PARKINSON DISEASE WITH CONSTIPATION**  **(SCREENING FORM)** | **[figure not shown]** |
| --- | --- | --- |

(Sticker)

Name :

IC No :

UKM MRN No :

Sex : Male / Female

Age :

Race : Malay / Chinese / Indian / Others

Religion : Islam / Buddhist / Hindu / Christian / Others

Body weight :

Height :

BMI :

Duration of Parkinson Disease:

Disease severity (MDS - UPDRS):

Fulfill Rome III Criteria – Constipation : YES/NO

|  | | | | | | |
| --- | --- | --- | --- | --- | --- | --- |
| Indicated the amount of fibre in your diet: | | | | |  | |
|  | Low (less than 3 servings per day) | | | |  | |
|  | Medium (3-5 servings per day) | | | |  | |
|  | High (more than 5 servings per day) | | | | *1 serving = ½ cup | |
|  |  | | | |  | |
| How often do you perform physical exercise? | | | | |  | |
|  | |  |  |  |  |  |
|  | Sedentary (less than 4 hour per week) | | | |  | |
|  | Non Sedentary (more than 4 hour per week) | | | |  | |
|  | | | | |  | |
| Current medications: | | |  | Previous colonoscopy(within 5 years) | | |
|  | | |  | Year | | Diagnosis |

| Fecal occult blood screening |
| --- |
|  |

| Name:  MRN:  (Sticker) |  | Day 0 |  |  |
| --- | --- | --- | --- | --- |
|  |  | Date | / / 2018 | |

**Rome III Criteria – Constipation Module^1^ (CONSTIPATION SCREENING FORM)**

| **Q1.** In the last 3 months, how often did you have discomfort or pain anywhere in your abdomen? | | |  | **Q11.** In the last 3 months, how often did you strain during bowel movements? | | |
| --- | --- | --- | --- | --- | --- | --- |
|  | Never |  |  |  | Never or rarely |  |
|  | Less than one day a month |  |  |  | Sometimes |  |
|  | One day a month |  |  |  | Often |  |
|  | Two to three days a month |  |  |  | Most of the time |  |
|  | One day a week |  |  |  | Always |  |
|  | More than one day a week |  |  |  |  |  |
|  | Every day |  |  |  |  |  |
|  | | |  |  |  |  |
| **Q2.** For women: Did this discomfort or pain occur only during your menstrual bleeding and not at other times? | | |  | **Q12.** In the last 3 months, how often did you have a feeling of incomplete emptying after the bowel movements? | | |
|  | No |  |  |  | Never or rarely |  |
|  | Yes |  |  |  | Sometimes |  |
|  | Does not apply because I have had the change in life (menopause) or I am a male |  |  |  | Often |  |
|  |  |  |  |  | Most of the time |  |
|  |  |  |  |  | Always |  |
|  | | |  |  |  |  |

| **Q3.** Have you had this discomfort or pain 6 months or longer? | | | |  | **Q13.** In the last 3 months, how often did you have a sensation that the stool could not be passed, (i.e. , blocked), when having a bowel movement? | | |
| --- | --- | --- | --- | --- | --- | --- | --- |
|  | No | |  |  |  | Never or rarely |  |
|  | Yes | |  |  |  | Sometimes |  |
|  |  | |  |  |  | Often |  |
|  |  | |  |  |  | Most of the time |  |
|  |  | |  |  |  | Always |  |
|  | | | |  |  |  |  |
| **Q4.** How often did this discomfort or pain get better or stop after you had a bowel movement? | | | |  | **Q14.** In the last 3 months, how often did you press on or around your bottom or remove stool in order to complete a bowel movement? | | |
|  | Never or rarely | |  |  |  | Never or rarely |  |
|  | Sometimes | |  |  |  | Sometimes |  |
|  | Often | |  |  |  | Often |  |
|  | Most of the time | |  |  |  | Most of the time |  |
|  | Always | |  |  |  | Always |  |
|  | | | |  |  |  |  |
| **Q5.** When this discomfort or pain started, did you have more frequent bowel movements? | | | |  | **Q15.** In the last 3 months, how often did you have difficulty relaxing or letting go to allow the stool to come out during a bowel movement? | | |
|  | Never or rarely | |  |  |  | Never or rarely |  |
|  | Sometimes | |  |  |  | Sometimes |  |
|  | Often | |  |  |  | Often |  |
|  | Most of the time | |  |  |  | Most of the time |  |
|  | Always | |  |  |  | Always |  |
|  |  | |  |  |  |  |  |
| **Q6.**  When this discomfort or pain started, did you have less frequent bowel movements? | | | |  | **Q16.** Did any of the symptoms of constipation listed in question 9-15 above begin more than 6 months ago? | | |
|  | | Never or rarely | |  |  | Yes |  |
|  | | Sometimes | |  |  | No |  |
|  | | Often | |  |  |  |  |
|  | | Most of the time | |  |  |  |  |
|  | | Always | |  |  |  |  |
|  | | | |  |  |  |  |
| **Q7.** When this discomfort or pain started, were your stools (bowel movements) looser? | | | |  | **Q17.** In the last 3 months, how often did you have loose mushy or watery stool? | | |
|  | | Never or rarely | |  |  | Never or rarely |  |
|  | | Sometimes | |  |  | Sometimes |  |
|  | | Often | |  |  | Often |  |
|  | | Most of the time | |  |  | Most of the time |  |
|  | | Always | |  |  | Always |  |
|  | | | |  |  |  |  |
|  | | | |  |  |  |  |

| **Q8.** When this discomfort or pain started, how often did you have harder stools? | |
| --- | --- |
|  | Never or rarely |
|  | Sometimes |
|  | Often |
|  | Most of the time |
|  | Always |
|  | |
| **Q9.** In the last 3 months, how often did you have fewer than three bowel movements (0-2) a week? | |
|  | Never or rarely |
|  | Sometimes |
|  | Often |
|  | Most of the time |
|  | Always |
|  | |
| **Q10.** In the last 3 months, how often did you have hard or lumpy stools? | |
|  | Never or rarely |
|  | Sometimes |
|  | Often |
|  | Most of the time |
|  | Always |

^1^Drossman et al *Rome III The Functional Gastrointestinal Disorders (3^rd^ Edition)*, August 2006

| Name:  MRN:  (Sticker) |  | Day 0 |  |  |
| --- | --- | --- | --- | --- |
|  |  | Date | / / 2018 | |

**Garrigues Survey – Constipation^1^**

|  |  | | | |  | |  | |  |  |  |
| --- | --- | --- | --- | --- | --- | --- | --- | --- | --- | --- | --- |
| **Q1.** Indicate your age. | | | | | | |  | | **Q11.** How often are your stools hard? | | |
|  | | | | |  | |  | |  | Never |  |
|  |  |  |  |  |  | |  | |  | Sometimes (less than 25% of time) |  |
|  |  |  |  |  |  | |  | |  | Often (more than 25% of time) |  |
|  |  |  |  |  |  | |  | |  | Always |  |
|  | | | | | | |  | |  |  |  |
| **Q2.** Indicate your gender. | | | | | | |  | | **Q12.** Do you feel a blockage in the anus that makes it difficult to pass the stool? | | |
|  | Male | | | |  | |  | |  | Never |  |
|  | Female | | | |  | |  | |  | Sometimes (less than 25% of time) |  |
|  |  | | | |  | |  | |  | Often (more than 25% of time) |  |
|  |  |  |  |  |  |  |  |  |  | Always |  |
|  |  | | | |  | |  | |  |  |  |
| **Q3.** Indicate your educational level | | | | | | |  | | **Q13.** Do you need to press around the anus or vagina to complete a bowel movement? | | |
|  | Primary | | | |  | |  | |  | Never |  |
|  | Secondary | | | |  | |  | |  | Sometimes (less than 25% of time) |  |
|  | Tertiary | | | |  | |  | |  | Often (more than 25% of time) |  |
|  | Postgraduate | | | |  | |  | |  | Always |  |
|  |  | | | |  | |  | |  |  |  |
| **Q4.** Indicate your job | | | | | | |  | | **Q14.** Do you spend more than 10 minutes on the toilet to pass the stools? | | |
|  | | | | | | |  | |  | Never |  |
|  |  |  |  |  |  |  |  | |  | Sometimes (less than 25% of time) |  |
|  |  |  |  |  |  |  |  | |  | Often (more than 25% of time) |  |
|  |  |  |  |  |  |  |  | |  | Always |  |
|  | | | | | | |  | |  |  |  |
| **Q5.** Indicate the amount of fibre in your diet | | | | | | |  | | **Q15.** How many bowel movements do you usually have each week? | | |
|  | Low (less than 3 servings per day) | | | |  | |  | |  | | |
|  | Medium (3-5 servings per day) | | | |  | |  | |  |  |  |
|  | High (more than 5 servings per day) | | | |  | |  | |  |  |  |
|  | *1 serving = ½ cup | | | |  | |  | |  |  |  |
| **Q6.**  How often do you perform physical exercise? | | | | | | |  | | **Q16.** Do you take oral laxatives? | | |
|  | | Never | | | | |  | |  | Never |  |
|  | | Sometimes (less than 3 times per week) | | | | |  | |  | Fewer than once a week |  |
|  | | Habitually (more than 3 times per week) | | | | |  | |  | One or more times a week |  |
|  | |  | | | | |  | |  | Every day |  |
|  | | | | | | |  | |  |  |  |
| **Q7.** Indicate which drugs you are taking | | | | | | |  | | **Q17.** Do you need to use suppositories to have bowel movements? | | |
|  | | Non steroidal anti inflammatory (NSAIDs) | | | | |  | |  | Never |  |
|  | | Anxiolytics | | | | |  | |  | Fewer than once a week |  |
|  | | Calcium channel antagonist | | | | |  | |  | One or more times a week |  |
|  | | Female hormone based drugs | | | | |  | |  | Every day |  |
|  | | |  |  | |  | |  |  |  |  |
|  | | | | | | |  | |  |  |  |
| **Q8.** Have you felt constipated? | | | | | | |  | | **Q18.** Do you need to use enemas to have bowel movements? | |  |
|  | | Yes | | | | |  | |  | Never |  |
|  | | No | | | | |  | |  | Fewer than once a week |  |
|  | |  | | | | |  | |  | One or more times a week |  |
|  | |  | | | | |  | |  | Every day |  |
|  | |  | | | | |  | |  |  |  |
| **Q9.** Do you strain during a bowel movement? | | | | | | |  | | **Q19.** Have you visited a doctor because of constipation? | |  |
|  | | Never | | | | |  | |  | Yes |  |
|  | | Sometimes (less than 25% of time) | | | | |  | |  | No |  |
|  | | Often (more than 25% of time) | | | | |  | |  |  |  |
|  | | Always | | | | |  | |  | |  |
|  | |  | | | | |  | |  |  |  |
| **Q10.** Do you feel an incomplete emptying sensation after a bowel movement? | | | | | | |  | | **Q20.** Have you presented with abdominal pain more than six times this past year? | |  |
|  | | Never | | | | |  | |  | Yes |  |
|  | | Sometimes (less than 25% of time) | | | | |  | |  | No |  |
|  | | Often (more than 25% of time) | | | | |  | |  |  |  |
|  | | Always | | | | |  | |  |  |  |
|  | |  | | | | |  | |  | |  |
|  | |  | | | | |  | | **Q21.** Have you presented with loose or watery stools? | |  |
|  | |  | | | | |  | |  | Yes |  |
|  | |  | | | | |  | |  | No |  |
|  | |  | | | | |  | |  |  |  |

^1^Garrigues et al *Am J Epidemiol* 2004

PDQ-39 (MALAY)

| Name:  MRN:  (Sticker) |  | Day 0 |  |  |
| --- | --- | --- | --- | --- |
|  |  | Date | / / 2018 | |

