**4. OBJECTIVE**

**4.1 PRIMARY OBJECTIVE**

- To determine the effects of probiotics (multistrains of Lactobacillus and Bifidobacterium ) on constipation among Parkinson disease patients compared to placebo
- To determine the effects of probiotics on Gastrointestinal Transit Time (GTT) compared to placebo

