|  | **6. HOSPITAL PROFILE/DEMOGRAPHIC**  **7. STUDY PERIOD**  June 2018 – June 2019  **8. SUBJECTS**  **8.1 TARGET POPULATION**  Patients with Parkinson disease attending the neurology outpatients clinic who fulfil inclusion and exclusion criteria  **9. SAMPLING**  **9.1 INCLUSION CRITERIA**   1. Idiopathic PD diagnosed using UK PD Society Brain Bank Criteria 2. Diagnosis of constipation according to Rome III Functional Constipation Criteria 3. Written informed consent   **ROME III Diagnostic Criteria : Functional Constipation**   \| Functional Constipation \| \| --- \| \| Must include 2 or more of the following:  Straining *  Lumpy or hard stools*  Sensation of incomplete evacuation*  Sensation of anorectal obstruction/blockage*  Manual manoeuvres to facilitate defecation(digital evacuation, support of pelvic floor)*  <3 defecation per week*  ***≥25% of defecations**  Loose stool rarely present without use of laxatives  Insufficient criteria for IBS \|   Based on Longstreth GF et al.Gastroenterology 2006 ;130:1480-1491  **9.2 EXCLUSION CRITERIA**   1. Secondary Parkinsonism 2. Previous history of small and large bowel disease 3. Previous extensive gastrointestinal tract surgery 4. Positive stool occult blood in the last 1 month 5. Use of probiotics or antibiotics in 2 weeks before baseline visit 6. Underlying Dementia 7. Hypothyroidism 8. Diagnosed with major depression and on antidepressant 9. Lactose intolerance   10. Type 1 and Type 2 DM  **10. DATA COLLECTION**  **10.1 METHOD OF DATA COLLECTION**  Patients with idiopathic PD attending the neurology outpatients’ clinic will be invited to participate in the study. All subjects will be screen for constipation by using Rome III Criteria – Constipation Module. Written informed consent will be obtained from all subjects after screening inclusion and exclusion criteria. Baseline demographic data will be recorded into a structured questionnaire.  Screening assessment :  1) Constipation screening using Rome III Criteria – Constipation Module  2) Fecal occult blood testing - negative test will be included in the study  The eligible subjects will be assess on the first visit as below :  1) Constipation symptoms by using Garrigues Constipation module (GQ)  2) Quality of life by using PDQ39 Questionnaire (self-administered malay version )  3) Parkinson Disease severity by using MDS-UPDRS  4)Non motor symptoms of PD by using NMS scale  (All the above questionnaires are validated)  Subsequently, subjects will be instructed to consume 4 red carmine capsule(food colourant) and once the stool turn red in colour, Gatrointestinal Transit Time(GTT) will be measured and recorded. Subjects will then receive a 3g sachet of either probiotics (containing multistrains of lactobacillus and Bifidobacterium 30 Colony Forming Unit) or placebo twice-daily for a duration of 8 weeks. Once consumption completed, subjects need to consume again another 4 red carmine capsule and GTT will be measured and recorded again. Final assessment will be done once subjects completed all the probiotics or placebo given(week 8) and subjects need to be assess again on constipation symptoms, non-motor symptoms, quality of life and disease severity same as done at baseline using the same questionnaire.  **10.2 STUDY PROTOCOL**  Randomization  All patients who fulfill inclusion and exclusion criteria will be stratified based on age, sex and background social economics. Patients who are enrolled will be randomized into two treatment groups which a probiotics group who will receive probiotics (containing multistrains of lactobacillus and Bifidobacterium 30 Colony Forming Unit) or placebo using blocks randomization method, in blocks of 4. Patients and investigator will remain blinded to the treatment protocol.  Following randomization, patients will receive their assigned treatment from the pharmacy department, Hospital Canselor Tuanku Muhriz, PPUKM  Treatment  Active treatment group will receive a 3 gram sachet of probiotics containing multistrains of lactobacillus and Bifidobacterium 30 Colony Forming Unit x 10^9^ to be taken twice daily for 8 weeks.  Composition of probiotics:   \| Lactobacillus acidophilus \| 107mg \| \| --- \| --- \| \| Lactobacillus casei \| 107mg \| \| Lactobacillus lactis \| 107mg \| \| Bifidobacterium bifidum \| 107mg \| \| Bifidobacterium infantis \| 107mg \| \| Bifidobacterium longum \| 107mg \|   Placebo group will receive a 3g sachet of substance (powder form) that has no therapeutic effect to be taken twice daily for 8 weeks.  All test products will be concealed in sealed envelopes, to ensure blindedness  **10.3 STUDY ASSESSMENT**  All patients will be assessed at baseline and week 8 for improvement in constipation symptoms using the Garrigues Constipation Questionnaire^35^, Quality of Life by using self- administered PDQ39 questionnaire (malay version)^36^, disease severity by using MDS-UPDRS and non-motor symptoms by using NMS scale . The Gastrointestinal transit time will be assessed at baseline and week 8 using red carmine capsule. Compliance to treatment, side effects and clinical assessments will be performed by a blinded assessor at baseline and week 8 for both groups.  **Gastrointestinal Transit Time Protocol**  Following randomization, subjects will be instructed to ingest 4 red carmine capsule after last bowel opening. Red carmine capsule is a food colorant and non-toxic to body which is used to measure GTT. The time of ingestion will be recorded. GTT is measured from the time of red carmine capsules consumption and first appearance of red colored stool. The duration from time of ingestion and appearance of red colored stool (Gastrointestinal transit time) will be recorded by patient at baseline, and week 8. The use of laxatives is not forbidden, but patients are required to use as per needed. GTT was measured during pre and end treatment in both groups.  **Constipation-Related Symptom Assessment**  Constipation related symptoms will be assessed using the Garrigues Constipation Questionnaire (GQ)^35^ which is a 21-item that was developed to define the presence of chronic constipation. Only 13 of the 21 items are related to bowel habits. The Rome 111 criteria were used to define constipation. The items are scored using two different four-point Likert scales. The first consisted of ‘never’, ‘sometimes’ (25% of the time) and ‘always’. The second consisted of ‘never’, ‘fewer than once a week’, ‘one or more times a week’ and ‘every day’. Total and cut off scores were not reported.  **Quality Of Life Assessment**  Baseline Quality of life patients will be assess using self-administered PDQ-39^36^ Questionnaire(Malay version) and end of intervention, subject will be assessed again using the same questionnaire. PDQ-39 questionnaire contains 39 items with each item was rated by the patients using one of five categories, from 0 (never) to 4 (always). PDQ-39 summary index (PDQSI) is calculated by dividing the sum of the total raw score by the maximum possible score (156 or 152 points, depending on the patient’s marriage status) and multiplying by 100. In this study, we will use PDQSI as a standardized index for representing PD patients’ life quality.  **Non Motor symptoms (NMS) assessment**  Severity of Non Motor symptoms of each individual will be assess using NMSS Questionnaire. Frequency and severity of each NMS are taken into account. Final total score of disability (0=no disability; 360=maximal disability).  **DDisease severity assessment**  Parkinson Disease severity assessment will be assess using MDS-UPDRS questionnaire. MDS UPDRS has four parts which include nonmotor experiences of daily living (13 items), motor experiences of daily living (13 items), motor examination (18 items), and motor complications (six items). Each subscale now has 0-4 ratings, where 0 = normal, 1 = slight, 2 = mild, 3 = moderate, and 4 = severe.  10.4 **VALIDITY OF TOOLS**  NMS and MDS-UPDRS are public domain questionnaire  Validated score : PDQ 39 (malay version)- permission obtained from author  Garrigues Constipation Questionnaire- awaiting permission from author  **11. STASTICAL ANALYSIS**  Statistical Package for the Social Sciences (SPSS) Software version 2 will be used for statistical analysis. Age, height, weight, body mass index (BMI) and gender were compared between the groups by Student’s t-test and the chi-squared test. General Linear Model will be used to compare intestinal transit time in probiotics and placebo groups before and after 8 weeks of intervention. Pre- and post-probiotics consumption data on clinical evaluation of constipation that will be obtained from all the questionnaires namely Rome III criteria, PDQ-39 Questionnaire and Garrigues Constipation Questionnaire will be analysed using Mc Nemar Test. Independent t-test will be used to compare the differences of intestinal transit time in both groups. Pearson correlation and Simple linear regression analysis will be utilized to explore the relationship and effect between two numerical variables. A p-value <0.05 will be considered as statistically significant.  **11.1 SAMPLE SIZE CALCULATION**  The sample size is being calculated based formula comparing between two proportions. Sample size calculation was performed according to a study by Sakai et al^32^ based on value reported on changes in percentage of bowel movements and complete bowel movements after 3 weeks of probiotics treatment where there was a significant decreased from 73.7% to 36.8%,  Formula for sample size comparing two proportions:  [figure not shown]  Sample size was estimated as follows :  p1 = 0.737  p2 = 0.368  zα = 1.96  zβ = 0.84  n = 0.737 (1 – 0.737) + 0.368 (1 – 0.368 ) X (1.96 + 0.84) ^2^  (0.737 – 0.368) ^2^  n = 0.193831 + 0.232576 X 7.84  0.136161  n = 25 per group  The number of samples per group is further added 20% to compensate for non-response and lost to follow up. The final samples required for each group is 30 patients. |

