# **Penyakit Parkinson Soal Selidik Mutu Hidup (PDQ-39)**

Disebabkan menghidap penyakit Parkinson,
berapa kerapkah dalam sebulan yang lalu telah anda…

Sila **tandakan satu kotak** bagi setiap soalan

|  |  |  | Tidak Pernah | Jarang-jarang sekali | Kadang-kadang | Sering | Selalu  atau tidak boleh lakukan langsung |
| --- | --- | --- | --- | --- | --- | --- | --- |
| 1. | Menghadapi kesukaran melakukan kegiatan riadah (kegiatan waktu lapang) yang ingin anda lakukan? |  |  |  |  |  |  |
| 2. | Menghadapi kesukaran menjaga rumah anda seperti kerja bertukang sendiri (tugas-tugas minor di dalam rumah seperti membina rak atau membaiki almari),  kerja rumah, memasak? |  |  |  |  |  |  |
| 3. | Menghadapi kesukaran mengangkat  beg-beg perbelanjaan harian? |  |  |  |  |  |  |
| 4. | Menghadapi masalah berjalan sejauh setengah batu (kira-kira 800 meter)? |  |  |  |  |  |  |
| 5. | Menghadapi masalah berjalan sejauh 100 ela (kira-kira 90 meter)? |  |  |  |  |  |  |
| 6. | Menghadapi masalah pergerakan  di dalam rumah semudah yang  anda inginkan? |  |  |  |  |  |  |

Sila periksa bahawa anda telah menandakan satu kotak bagi setiap soalan
sebelum meneruskan dengan muka surat yang berikutnya.

**Disebabkan menghidap penyakit Parkinson,**berapa kerapkah dalam sebulan yang lalu telah anda…

Sila **tandakan satu kotak** bagi setiap soalan

|  |  |  | Tidak Pernah | Jarang-jarang sekali | Kadang-kadang | Sering | Selalu  atau tidak boleh lakukan langsung |
| --- | --- | --- | --- | --- | --- | --- | --- |
| 7. | Menghadapi kesukaran berjalan-jalan  di tempat awam? |  |  |  |  |  |  |
| 8. | Memerlukan seseorang untuk menemani anda semasa anda keluar? |  |  |  |  |  |  |
| 9. | Berasa takut atau bimbang tentang kemungkinan anda tersungkur atau terjatuh di tempat awam? |  |  |  |  |  |  |
| 10. | Terkurung di dalam rumah lebih dari  apa yang anda inginkan? |  |  |  |  |  |  |
| 11. | Menghadapi kesukaran membersihkan diri anda? |  |  |  |  |  |  |
| 12. | Menghadapi kesukaran memakai  pakaian sendiri? |  |  |  |  |  |  |
| 13. | Menghadapi masalah membutangkan pakaian anda atau mengikat tali kasut? |  |  |  |  |  |  |
| 14. | Menghadapi masalah untuk menulis dengan jelas? |  |  |  |  |  |  |

Sila periksa bahawa anda telah menandakan satu kotak bagi setiap soalan
sebelum meneruskan dengan muka surat yang berikutnya

Disebabkan menghidap penyakit Parkinson,
berapa kerapkah dalam sebulan yang lalu telah anda…

Sila **tandakan satu kotak** bagi setiap soalan

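### The Garrigues form is repeated unchanged at week 8 with no recall period matched to treatment: Q8, Q19 and Q20 can show little or no improvement, and the other symptom items are blurred

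*Combined protocol and SAP*

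**What the plan says.** Section 4.1 lists two primary objectives. The first is "To determine the effects of probiotics (multistrains of Lactobacillus and Bifidobacterium ) on constipation among Parkinson disease patients compared to placebo"; the second concerns gastrointestinal transit time. For symptoms, section 10.3 states: "All patients will be assessed at baseline and week 8 for improvement in constipation symptoms using the Garrigues Constipation Questionnaire". Section 10.1 says the final assessment uses the same questionnaires as at baseline, and the flow chart shows the Garrigues form as the constipation assessment at both visits. No week-8 version with different wording is described. Under section 10.2 the sachets are "to be taken twice daily for 8 weeks".

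Section 10.3 describes the form as one "which is a 21-item that was developed to define the presence of chronic constipation". It adds that 13 of the 21 items concern bowel habits, without listing them, and that no total or cut-off score was reported. Section 11 sends the pre/post data from Rome III, the PDQ-39 and the Garrigues form to a McNemar test and does not say which Garrigues items are used.

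On the form in the appendix, Q20 asks "Have you presented with abdominal pain more than six times this past year", Q19 asks "Have you visited a doctor because of constipation" with no period, and Q15 asks "How many bowel movements do you usually have each week". By contrast, the Malay PDQ-39 in the same packet fixes a past-month window: "berapa kerapkah dalam sebulan yang lalu telah anda".

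**The concern.** A form designed to classify someone as chronically constipated is being used to measure change over eight weeks. For change, each answer at week 8 should describe a period on treatment. If it describes a period lying mostly before treatment, or a whole history, a patient who has improved can correctly give the baseline answer again. This applies in both arms, so it pulls the observed difference toward zero. The form carries the symptom evidence for the first primary objective, so a null result on constipation could come from the wording of the questions as well as from the product.

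**Working it through.** **The plan's own figure.** The plan computes nothing on recall. Its one calculation is the sample size: [0.737 × 0.263 + 0.368 × 0.632] × (1.96 + 0.84)² / (0.737 − 0.368)² = 0.426407 × 7.84 / 0.136161 = 24.55, rounded up to 25, and 25 × 1.2 = 30 per group. It reproduces. It uses proportions from an external fermented-milk study and no Garrigues item, so it is not affected here.

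**Time frames on the form.** Q1 to Q7 are background (age, sex, education, job, fibre, exercise, drugs). The other 14 items divide as follows.

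| Items | Number | Period printed | Can the answer change by week 8? |
|---|---|---|---|
| Q20 | 1 | past year | rarely |
| Q8, Q19 | 2 | none (yes/no) | not from yes to no, if read literally |
| Q21 | 1 | none (yes/no) | yes, from no to yes |
| Q15 | 1 | usual week | yes, but period blurred |
| Q9–Q14, Q16–Q18 | 9 | none (present-tense frequency) | yes, but period undefined |

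**Q20, overlap.** With 8 weeks of treatment, the share of the one-year window lying before treatment is (52 − 8)/52 = 44/52 = 85%. The share on treatment is 8/52 = 15%.

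**Q20, evenly spaced episodes.** Suppose pain is abolished from the first day. A patient with r episodes a year then has r × 44/52 in the window at week 8. Yes becomes no only if r exceeds 6 and r × 44/52 is at most 6, that is r ≤ 6 × 52/44 = 7.09.

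**Q20, random episodes.** With a Poisson count, P(yes) = 1 − P(count ≤ 6). The mean is r at baseline, r × 44/52 at week 8 if pain is abolished, and r × 48/52 if it is halved. The documents give no episode rate, so r is an assumption, shown over a range.

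| r per year | P(yes) baseline | week 8, pain halved | week 8, pain abolished |
|---|---|---|---|
| 7 | 0.550 | 0.467 | 0.381 |
| 10 | 0.870 | 0.813 | 0.740 |
| 12 | 0.954 | 0.924 | 0.879 |
| 20 | 1.000 | 0.999 | 0.998 |

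Even complete relief moves P(yes) by at most about 17 percentage points over this range (0.550 − 0.381), by 7.5 points at 12 a year, and by almost nothing at 20.

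**Q8 and Q19.** Let b be the number of patients going from yes to no and c the number going from no to yes. The McNemar statistic is (b − c)²/(b + c). If a past yes stays true, b = 0, and the item can show only worsening or nothing. Every participant meets Rome III constipation criteria at entry, so Q8 should be yes for nearly everyone at baseline, which leaves c near zero too.

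**Q9 to Q18.** If a share k of patients answer for their long-term state, the observed difference is (1 − k) times the true one. The documents give no basis for any value of k, so I put no number on this.

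**Rome III as a fallback.** Section 11 lists it for pre/post analysis, but 10.3 and the flow chart do not schedule it at week 8. Its form asks about the last 3 months; taking these as 13 weeks, (13 − 8)/13 = 5/13 = 38% of the window would still precede treatment.

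**The case against.** The strongest reply is that most of the form works. A reader might infer that the questionnaire as a whole cannot detect an eight-week effect. The documents do not support that. Nine of the 14 items, including straining, incomplete emptying, hard stools, blockage and laxative use, are in the present tense and can move. The word 'usually' in Q15 blurs the period but does not stop the count changing. Q20 can flip near its threshold. Rome III entry requires loose stool to be rare without laxatives, so many patients could truthfully answer no to Q21 at baseline and yes at week 8. That 'ever' is the natural reading of Q8 and Q19 is also an inference: the form prints no such word. All of this stands and limits the point.

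A reader might also infer that fixed items add noise to the others. They do not. No total score is defined, and under an item-wise McNemar test a patient fixed at yes contributes no discordant pair. Such items are uninformative and leave the rest untouched.

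Q20 may lie outside the 13 bowel-habit items. If those 13 all fall within Q8 to Q21, exactly one of the 14 is left out, and abdominal pain is the natural candidate. But the 13 are not listed, and section 11 does not confine the analysis to them.

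Finally, section 10.1 calls the questionnaires validated, and rewording departs from the published instrument. That is a real cost. Choosing items in the analysis plan would deal with Q19 and Q20 without rewording, but it would leave the missing window on Q8 to Q18 and Q21 as it is.

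**Conclusion.** The concern holds in limited form and should be fixed before the forms are used. The scheduled constipation-symptom measure has no item with a recall period matched to treatment. Q20 is nearly inert: 85% of its window precedes treatment at week 8, and with evenly spaced episodes only patients with more than 6 and at most 7.09 episodes a year would flip under complete relief. Q8 and Q19, read literally, cannot show improvement. The remaining symptom items can change, but an undefined period invites answers about the long-term state.

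The Q20 figures assume that treatment starts at baseline and runs the full 8 weeks, and the Poisson rates are my assumption. The statement on Q8 and Q19 rests on a literal reading of undated questions.

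Two stronger conclusions are tempting. A reader might infer a definite loss in percentage points or power by shrinking the 36.9-point difference (73.7% − 36.8%) used for the sample size. That difference comes from an external study, no Garrigues contrast is planned for, and the share of patients answering for their long-term state is unknown, so the dilution cannot be quantified and the sample size is not shown to be wrong. A reader might also call the form the primary endpoint. No primary endpoint is formally designated; transit time is a second primary objective, and this point does not touch it.

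**What to change.** - Print the same recall instruction, for example 'In the last 4 weeks', above Q8 to Q18 and Q21 on both the baseline and the week-8 form. This matches the PDQ-39 month. At week 8 the window then covers weeks 5 to 8, all on treatment.
- Ask Q15 as the number of bowel movements in the last 7 days.
- Collect Q19 and Q20 at baseline only, and exclude them from the pre/post outcome set.
- State in section 11 which Garrigues items form that set.

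The cost is a small departure from the published wording, which should be disclosed when results are reported. No published total or cut-off score is lost, because section 10.3 notes that none was reported. Section 10.4 shows that the author's permission is still awaited, so the changes can go into that request; the author would need to accept them. Visits, sample size and treatment are unaffected.
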